### 2.4 Recruitment and study conduct

Initially, selected individuals will be contacted by a postal cover letter including general information on the panel, the data protection and privacy concept, the questionnaire for the first survey wave as well as a consent form. Participants are therein requested to give informed consent for participation in the panel for its entire duration. Letters to the individual participants are addressed and sent by the Data Trust Office of Technische Universität (TU) Dresden (see below) in order to ensure separation of the participants’ personal information and their responses in the questionnaire. Only those participants sending back a signed consent form will subsequently be included in the panel. All return letters are collected at the project office within the responsible institute, where questionnaire and consent forms are separated. The latter are collected and managed by the Data Trust Office.

The questionnaire will be presented in paper and will also be available as an online version. The printed questionnaire will be created using the software FormPro and the digital questionnaire will be created using the software REDCap. Participants choosing the latter option will find an individualized link to the online questionnaire within the recruitement papers. A stamped return envelope is included in the initial contact letter for participants deciding to complete the questionnaire on paper. Data entry from printed questionnaires is largely automated using FormPro software. The accuracy of the readings is checked manually.

In case of a response rate lower than 15%, advertisement in official publications of the major’s offices in the included communities will be placed, explaining the purpose of the panel and stressing the fact that participation is a means for citizens to be heard on such an important issue as health care planning.

### 2.5 Data security, privacy and ethics

The data security concept was developed by the project team and reviewed by the data security office of the Medical Faculty Carl Gustav Carus at the TU Dresden and the federal data security office of Saxony. According to the concept, the completed questionnaires–if they were filled out on paper–are digitized and stored on secure servers, separately from the person-identifying data. Person-identifying data, such as names and addresses, are only stored at the Data Trust Office of the TU Dresden, allowing the office to contact the participants for each wave. It is not possible to draw any conclusions from the participants’ details to their person during data analysis. This is ensured by coding/pseudonymization. Study staff will not have access to the coding list at any time. It is exclusively created and maintained by the independent Data Trust Office of the TU Dresden.

Ethics approval for this panel survey was granted by the ethics committee of the TU Dresden in September 2022 (No BO-EK-320072022). The study protocol has been registered at the German Clinical Trials Register as the German WHO primary registry in March 2023 (study registration number DRKS00031229).

### 2.6 Status and timeline

Fig 2 depicts the timeline for the panel survey. The survey is designed as an open-ended project.

**Fig 2 pone.0310656.g002:**

Timeline. In 2022, the questionnaire and the data security concept were designed and ethics approval was obtained. Pretests were conducted in 2023. Survey waves are planned every two years, starting in 2024. Intermediate surveys on focus topics are possible.

### 2.7 Statistical plan

Seeing as the panel is not designed to test hypotheses and thus no confirmatory research questions were designed, data analysis will be primarilay descriptive. Additionally, changes over time will be visualized in graphical form. Apart from that, appropriate statistical models will be used to analyze changes in the domains covered by each questionnaire. Thus, Analyses of Variance (ANOVAs) and t-tests will be regularily conducted, should a normal distribution be present. Otherwise, non-parametric alternatives such as the Mann-Whitney-U- or Kruskall-Wallis test will be used. In order to analyze relationships between domains, appropriate correlation measures will be computed with respect to the data available and tests for normal distribution (Cramer’s V for nominal scales, Spearman’s r or Kendall’s tau b for ordinal scales, Pearson’s r for metric scales). Where literature suggests causal inferences are likely, Regression models or Strcutural Equation Modelling for latent constructs will be used.

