**Discussion and outlook:**

The results are intended to identify gaps in health care and to develop patient-centered health care goals for the region together with stakeholders in Saxon health care planning. At the same time, longitudinal data allow mapping of perceived health status and perceived health care trends.

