### 1.1 Rationale

Saxony is one of the German federal states with the highest average age. Of its four million people population, 27% are older than 65 years (reference 2021) and Saxony has the 6^th^ lowest birthrate of all German federal states (1.527 in 2021) [14]. The proportion of the age group older than 65 years is lowest in and around the cities of Leipzig and Dresden and highest in more rural areas, sometimes reaching over 30% (e.g. in the districts of Görlitz, Zwickau, Vogtland, Central Saxony). At least partly, the latter are also the regions where density of physicians and probability of setteling new physicians is lowest [15]. This is of particular importance as the proportion of doctors reaching retirement age in the near vicinity (those who are already over 59 years old) varies between 50% and 75% throughout Saxony [15]. The expectedly decreasing number of physicians meets a growing demand for health care. An increase in the number of patients with diabetes mellitus, hypertension, dementia or oncological diseases is predicted for almost all regions of Saxony [15]. Additionally, Saxony had the 3^rd^ largest death rate of all German federal states, independent of the cause of death (1,480 deaths per 100,000 citizens in 2022) [14].

Panel surveys are longitudinal studies researching the same sample time and again over a potentially open-ended time period. By collecting longitudinal data on the topics raised above, panel surveys allow i) for mapping changes in the assessment of various outcomes at aggregate and individual data levels [16], ii) for avoiding measurement bias due to single points of measurement [17] and iii) for conducting causal analyses on the effectiveness of health care interventions (if intervention and control groups are formed) (see e.g. [18]). Hence, panel surveys contribute to the development of political agendas and their alignment with the reality of citizens’ lives throughout Europe. For example, data from the European Social Survey, which explicitly covers health and well-being every two years, are widely used to assess social determinants of health, which is a prerequisite for targeted social policies [19]. The Health Survey for England, conducted regularly by the NHS, allows e.g., for determining predictors of health care access as well as health outcomes [20]. However, none of the panel questionnaires mentioned above cover issues releated to the perceived quality of health care delivery within a region.

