### 1.2 Objective

Therefore, we aim to conduct a structured and longitudinal survey of perceived health status and perceived quality of health care of citizens in Saxony as the first health care panel for Saxony. The panel data can serve as a basis for the systematic derivation of health care goals and target group-specific, regionally appropriate preventive measures and interventions to maintain or improve the quality of care in the region.

The panel’s overarching research questions are:

What is the relationship between perceptions of health status, quality of health care and quality of life?Do individual (health) behavior, use of health care facilities, medical diagnoses, work environment and socio-demographic factors influence perceptions of health status, quality of health care and quality of life?How do perceptions of health status, quality of health care and quality of life change over time?

A general overview of the domains and research questions is depicted in Fig 1.

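### The tests named for change between waves do not use the panel's pairing, so selective drop-out can be read as change in perceived health

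*Protocol article*

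**What the plan says.** Section 1.2 asks "How do perceptions of health status, quality of health care and quality of life change over time", and the abstract promises that "longitudinal data allow mapping of perceived health status and perceived health care trends". The design is a true panel: section 1.1 explains that "Panel surveys are longitudinal studies researching the same sample time and again over a potentially open-ended time period" and gives the mapping of individual-level as well as aggregate change as a reason for choosing it. Entry is fixed at first contact: "Only those participants sending back a signed consent form will subsequently be included in the panel" (section 2.4). The Fig 2 legend adds "Survey waves are planned every two years, starting in 2024", and section 2.6 states "The survey is designed as an open-ended project". The article describes no refreshment sample.

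On analysis, section 2.7 says "Additionally, changes over time will be visualized in graphical form" and that "appropriate statistical models will be used to analyze changes in the domains covered by each questionnaire". It then becomes specific: ANOVA and t-tests if the data are normally distributed, otherwise tests such as Mann-Whitney U or Kruskal-Wallis. It does not say whether the t-tests and ANOVA are paired or repeated-measures. It does not say whose answers each wave's graph will show.

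**The concern.** Mann-Whitney U and Kruskal-Wallis compare separate groups of people. If the groups are waves, a person who answers twice is treated as two unrelated people, and a person who leaves simply disappears from the later group. The comparison then mixes two things: people whose answers changed, and a different mix of people answering. The link between a member's answers, which is the reason for running a panel, is not used.

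The stake is the trend itself. The discussion presents the panel as a basis for regional health care goals and as part of continuous monitoring. A shift of several points that reflects only who stayed could be taken for a real change in the population's health. In an open-ended panel without refreshment, such a shift accumulates for as long as retention differs in the same direction. Calling the analysis mainly descriptive does not help, because the descriptive trend carries the same bias.

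**Working it through.** **The plan's own figures.** Section 2.2 states n = 2,196 for OR 1.50, prevalence 20%, power 90% and two-sided alpha 5%. An odds of 0.25 × 1.5 = 0.375 gives a second proportion of 0.375/1.375 = 27.27%. A two-proportion calculation of 20% against 27.27% with a 4:1 split gives 1,760 + 440 = 2,200, within 0.2% of 2,196. The 4:1 split is an assumption, as the article does not state it. The contact figures are exact: 2,196/0.15 = 14,640, and 15,000 × 0.15 = 2,250.

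**Inputs for the illustration.**
- From the article: 20% limited in activity (section 2.2) and N = 2,250 at wave 1.
- Assumed: retention r_L among limited and r_N among non-limited members, and no individual changes status.

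**Formulas.**
- Share seen at wave 2: q = 0.20·r_L / (0.20·r_L + 0.80·r_N)
- Respondents at wave 2: n2 = 2,250 × (0.20·r_L + 0.80·r_N)
- Unpaired z = (q − 0.20) / √(0.20·0.80/2,250 + q(1−q)/n2)

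On a yes/no item this is practically the comparison that a Mann-Whitney test makes. The z is what an unpaired test would report. It ignores that the same people appear in both waves.

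| r_L / r_N | n2 | q | Apparent change (points) | z |
|---|---|---|---|---|
| 80% / 80% | 1,800 | 0.16/0.80 = 20.0% | 0 | 0 |
| 70% / 80% | 1,755 | 0.14/0.78 = 17.9% | −2.1 | −1.65 |
| 65% / 80% | 1,733 | 0.13/0.77 = 16.9% | −3.1 | −2.53 |
| 60% / 80% | 1,710 | 0.12/0.76 = 15.8% | −4.2 | −3.45 |
| 70% / 60% | 1,395 | 0.14/0.62 = 22.6% | +2.6 | +1.84 |

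True change is zero in every row. If the 60%/80% pattern repeats, wave 3 shows 0.072/0.584 = 12.3% and wave 4 shows 0.0432/0.4528 = 9.5%.

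**Paired completers.** Each stayer's difference from their own earlier answer is zero, so the mean change is exactly 0 under any retention pattern. The artefact belongs to the unpaired route. The paired result describes stayers only.

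**Retention weighting.** In the 60%/80% case, weighting each wave-2 respondent by 1/retention gives 0.12/0.60 = 0.20 limited and 0.64/0.80 = 0.80 not limited, so the share returns to 20.0%.

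**Death alone.** Section 1.1 gives 1,480 deaths per 100,000 in a year, so two years remove 1 − 0.9852² = 2.9%. If limited members die at three times the rate of others (an assumption), the others' two-year risk is 0.0294/1.4 = 2.1% and that of the limited is 6.3%. The share becomes 0.20 × 0.937/0.9706 = 19.3%.

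**Care ratings through the health route.** If limited members rate care 0.3 SD lower or higher than others (an assumption), the 60%/80% case moves the mean by (0.158 − 0.20) × (∓0.3) = ±0.013 SD.

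**The case against.** The strongest reply is that the article does not commit to the faulty comparison. It promises appropriate models without naming them, and its list of non-parametric tests is given as examples. T-tests and ANOVA can be paired or repeated-measures. Section 2.3 plans to compare changes between municipalities or districts, for which independent-group tests are suitable. A journal article is also condensed, and rules for missing waves, weights and tables of leavers may stand in a fuller plan.

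Much of this stands. The absence of an attrition plan is not the point here. A reader might infer that every plot and test will use whoever happens to answer each wave, but the text does not say so. What remains is that the article does name methods for change, that the named fallback tests cannot be paired, and that no within-person method is named for change.

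A reader might also infer that health-related drop-out and death will make health and care appear to improve. The article does not support this, for three reasons:
- It gives no retention figures, and the sign depends on who leaves. Reversed retention shows worsening.
- People who die also leave the living population, so a shift through death is partly real. At the article's crude rate it is small.
- For care ratings, the shift through health alone is negligible and of unknown sign. A larger one would need drop-out tied directly to how people rate care, which nothing here quantifies.

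**Conclusion.** The point holds as a fault in the stated method. If the named independent-sample tests, or raw wave graphs, are used to compare waves, they can present selective drop-out as change in perceived health, in either direction. For a 20% item with no individual change, the apparent shift at wave 2 runs from none (equal retention) through −2.1 points (70% against 80%, not significant) to −4.2 points (60% against 80%, z about −3.5). These sizes rest on assumed retention and on no refreshment of the panel. They show what the method permits and do not forecast what will happen. Pairing alone removes the artefact in this example, so the example does not show that weights are indispensable. Their role is to check whether a result resting on stayers carries over to the panel that was recruited. The point deserves correction before the second wave is analysed, because the trend is a stated product of the panel.

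**What to change.** In section 2.7:
- Base wave-to-wave change on a person-level longitudinal model that keeps every member with at least one wave: a mixed model, with a logistic version for yes/no items.
- Plot model-based wave means, or state for each raw plot whose answers it shows.
- As a sensitivity analysis, weight later waves for retention among members not known to have died, using wave-1 age, gender, perceived health, care rating and cluster. The first four fall within the questionnaire domains in section 2.1, and cluster is known from the sampling. An activity-limitation item could be added if the questionnaire contains one. Section 2.2 uses it only as a planning example, and the questionnaire is not shown.
- Tabulate wave-1 values of stayers and leavers beside each trend, with deaths separate where known.
- Keep the independent-group tests for comparisons between districts or other separate groups.

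The cost is a few sentences, some analysis code and somewhat wider intervals. Counting deaths may take more: the article describes no way of learning of them, and identities are held only by the Data Trust Office (section 2.5). That table should therefore be limited to deaths that become known.

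### The non-parametric tests that Section 2.7 names for analysing change assume independent groups, but the panel measures the same people in every wave

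*Protocol article*

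**What the plan says.** The third research question in Section 1.2 is about change: "How do perceptions of health status, quality of health care and quality of life change over time". Section 1.1 describes the design with "Panel surveys are longitudinal studies researching the same sample time and again over a potentially open-ended time period" and lists among the benefits of a panel that it allows "for mapping changes in the assessment of various outcomes at aggregate and individual data levels".

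The conduct sections fit that description. In Section 2.4, "Participants are therein requested to give informed consent for participation in the panel for its entire duration". In Section 2.5 the Data Trust Office alone keeps the coding list and contacts participants for each wave; on separating answers from identity the article says "This is ensured by coding/pseudonymization". Waves are planned every two years from 2024 (Section 2.6).

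Section 2.7 calls the analysis mainly descriptive and then says that "appropriate statistical models will be used to analyze changes in the domains covered by each questionnaire". The next sentence draws the consequence: "Thus, Analyses of Variance (ANOVAs) and t-tests will be regularily conducted, should a normal distribution be present". The one after covers the remaining case: "Otherwise, non-parametric alternatives such as the Mann-Whitney-U- or Kruskall-Wallis test will be used". Relationships between domains come later, with their own correlation measures, and regression or structural equation models follow. No paired test, repeated-measures method, mixed model or GEE is named anywhere in the article.

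**The concern.** Two waves of a panel give two answers from each person who stays in, and those answers are correlated. Mann-Whitney U and Kruskal-Wallis treat all observations as independent and have no paired form. An analyst who takes Section 2.7 at its word and compares wave 1 with wave 2 by Mann-Whitney U would use the wrong variance. Items on perceived health or quality of care that are ordinal or skewed would fall into this branch.

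At stake are the p-values and intervals for research question 3. With positive within-person correlation the variance is overstated, so real changes are missed. The results are meant to support regional health care goals, so a change wrongly reported as absent has a cost even in an exploratory study.

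**Working it through.** **The plan's own figure.** Section 2.2 requires n = 2,196 for OR 1.50, 20% prevalence, 90% power and two-sided alpha of 5%. Odds of 0.25 × 1.5 = 0.375 give a second proportion of 0.375/1.375 = 0.2727. If 20% of the sample is exposed (my assumption; the article does not say), a two-proportion calculation gives 2,200 in total and a logistic formula for a binary covariate gives 2,199, both close to 2,196. Equal groups would give only 1,432. The contact figure is exact: 2,196/0.15 = 14,640. This calculation concerns an association at one time point. It contains no between-wave correlation and does not size research question 3.

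**Inputs for the check.** The same n people answer in both waves, with equal SD in each and between-wave correlation r. The article gives no r, so 0.3, 0.5 and 0.7 are assumed.

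**Variance.** For the difference in wave means the true variance is 2(1 − r)SD²/n. An independent-sample test uses 2SD²/n. Its standard error is therefore too large by 1/√(1 − r), and under no change its test statistic has variance 1 − r instead of 1.

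**Type I error.** 2 × [1 − Φ(1.96/√(1 − r))].

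**Power.** Take the change that a paired test detects with 90% power, which lies 1.96 + 1.2816 = 3.2416 true standard errors from zero. The independent-sample test rejects only beyond 1.96/√(1 − r) true standard errors, so its power is Φ(3.2416 − 1.96/√(1 − r)).

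| r | SE too large by | 1.96/√(1 − r) | True type I error | Power (paired = 90%) |
|---|---|---|---|---|
| 0.3 | 1.20 | 2.343 | 1.9% | Φ(0.899) = 82% |
| 0.5 | 1.41 | 2.772 | 0.56% | Φ(0.470) = 68% |
| 0.7 | 1.83 | 3.578 | 0.035% | Φ(−0.337) = 37% |

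**Detectable change.** With 2,196 people in both waves, the change detected with 90% power is (1.96 + 1.2816)√(2(1 − r)/2,196) SD for the paired test and (1.96 + 1.2816√(1 − r))√(2/2,196) SD for the independent one:

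- r = 0.3: 0.082 against 0.092 SD
- r = 0.5: 0.069 against 0.087 SD
- r = 0.7: 0.054 against 0.080 SD

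**Rank tests.** The formulas above are for means. A simulation of a 5-point item (2,196 pairs, 3,000 runs, latent shift set to give 90% power to the paired t-test) shows the same pattern for the tests actually named. Signed-rank against Mann-Whitney power was 86% against 75% at r = 0.3, 84% against 60% at r = 0.5, and 81% against 30% at r = 0.7. With no shift, Mann-Whitney rejected in 2.3%, 0.9% and 0.2% of runs.

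**The case against.** The strongest reply is that Section 2.7 commits to less than it seems to. It speaks of appropriate models; t-tests and ANOVAs have paired and repeated-measures forms; and the two rank tests are only examples. In a condensed article, the paired form of a t-test can reasonably be left to the full plan. This stands for the parametric branch, which is merely unspecified. It does not clear the non-parametric branch, where both examples are independent-sample tests and the text leads to them from the analysis of change.

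The rank tests also have a legitimate use. Section 2.3 foresees comparing changes in coverage between municipalities or districts, and a Kruskal-Wallis test on individual change scores across regions would be valid and would use the pairing. Section 2.7 does not restrict the tests to that use, so the ambiguity remains.

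The practical effect is limited. At the planned sample size either approach detects changes below 0.1 SD, the error is conservative and creates no false positives, and the loss is modest at r = 0.3. All of this stands and bears on how serious the point is.

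A reader might infer that individual-level change will not be analysed at all. The article does not support that: regression and structural equation models are also listed and could address it. A reader might also infer that planned power is lost. Section 2.2 claims none for research question 3, so there is no planned figure to lose.

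**Conclusion.** The point holds for the non-parametric branch: the only such tests named in connection with change do not fit repeated answers from the same people. For t-tests and ANOVAs the form is left open. It would go too far to say that the plan prescribes unpaired analysis of all change.

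Used to compare waves, the named tests give p-values and intervals that are too conservative, to the extent shown in the table. Those figures assume a positive correlation of 0.3 to 0.7, equal SDs and the same respondents in both waves. With dropout, fewer people contribute a pair, so a purely paired test gains less.

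This should be fixed but is not critical. The analyses are exploratory, and sampling and data collection are unaffected. With two-yearly waves from 2024, the first between-wave test falls after the 2026 wave.

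**What to change.** In Section 2.7, separate comparisons of waves from comparisons of people.

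- **Change between waves:** paired t-test or Wilcoxon signed-rank test for two waves; repeated-measures ANOVA or Friedman test for three or more. Alternatively, a mixed model or GEE of the type suited to the outcome, with wave as a fixed effect and the participant accounted for. The model-based option also keeps people who miss a wave.
- **Comparisons between people:** keep Mann-Whitney U and Kruskal-Wallis for groups within one wave, or for individual change scores compared between regions or groups.

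The cost is a few sentences and slightly more analysis code. No new data are needed, provided the pseudonym stays the same across waves. The arrangements in Section 2.5 appear to allow this, and one added sentence should confirm it.
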